### Personal health profile

After completion of the baseline dementia risk assessment (including the data entry of the physical examination and laboratory measurements), a personal health profile is automatically provided in the personal account of the participants (My Demin). The personal health profile gives an overview of the presence of the risk and protective factors for dementia, without including the weight of the risk and protective factors. According to the Lifestyle for Brain Health (LIBRA) score, each risk and protective factor^19 52 53^ is categorised into one of the following categories: (1) room for improvement, (2) remember to manage well, (3) keep this up (see table 2). The ‘keep this up’ category represents factors that participants are currently managing well or diseases they do not have. The ‘room for improvement’ category represents the factors that could be improved by health behaviour change (eg, quit smoking, become more physical active, change diet, drink less alcohol). The category ‘remember to manage well’ is assigned when a risk factor (ie, cardiovascular diseases, hypertension, high cholesterol, diabetes mellitus, renal dysfunction and depression) is present, but the disease is managed well as participants have regular meetings with their general practitioner for disease control (diabetes mellitus) or use medication for disease management (cardiovascular diseases, hypertension, high cholesterol, renal dysfunction and depression) (see figure 1).

**Figure 1 F1:**
[figure not shown]
An example of a personal health profile.

**Table 2 T2:** Definition for the three categories in the personal health profile at baseline

Modifiable risk factors	Keep this up	Remember to manage well	Room for improvement
Diet	MIND-diet score=14 points	NA	MIND-diet score<14 points
Alcohol consumption	Average number of units of alcohol per week≤7 and number of units per day is: ≤3 for women or ≤4 for men	NA	Average number of units of alcohol per week>7 or number of units per day is: >3 for women or >4 for men
Cognitive activity	Paid working hours≥24 or CRIq score≥50	NA	Paid working hours<24 and CRIq score<50
Physical activity	(MVPA/week≥150 and sitting time≤8 hours/day) or (MVPA/week<150 and sitting time<4 hours/day)	NA	Sitting time>8 hours/day or (sitting time≥4 hours/day and MVPA/week<150)
Smoking	Past or never smoker	NA	Current smoker
Loneliness	De Jong Gierveld score<2	NA	De Jong Gierveld score≥2
CVD	No CVD	At least one CVD and receives medical treatment	At least one CVD and no medical treatment
Weight	BMI≥18.5 and BMI<25.0	NA	BMI<18.5 or BMI≥25.0
Blood pressure	DBP<90 mmHg and SBP<140 mmHg and no medical treatment	DBP<90 mmHg and SBP<140 mmHg and medical treatment	DBP≥90 mmHg or SBP≥140 mmHg
Cholesterol	LDL≤2.5 mmol/L and TC/HDL≤5 mmol/L and no medical treatment	LDL≤2.5 mmol/L and TC/HDL≤5 mmol/L and medical treatment	LDL>2.5 mmol/L or TC/HDL>5 mmol/L
Diabetes mellitus	Glucose<7.0 mmol/L and HbA1C≤53 mmol/mol	(HbA1C≤53 mmol/mol and medical treatment) or (glucose<7.0 mmol/L and HbA1C>53 mmol/mol and medical treatment)	(HbA1C>53 mmol/mol and no medical treatment) or (glucose≥7.0 mmol/L and HbA1C>53 mmol/mol) or (glucose≥7.0 mmol/L and HbA1C≤53 mmol/mol and no medical treatment)
Kidney	eGFR≥60 mL/min/1.73 m^2^	eGFR<60 mL/min/1.73 m^2^ and medical treatment	eGFR<60 mL/min/1.73 m^2^ and no medical treatment
Depression	CES-D<16 points	CES-D≥16 points and medical treatment	CES-D≥16 points and no medical treatment

BMI, body mass index; CES-D, centre for epidemiological studies depression scale; CRIq, cognitive reserve index questionnaire; CVD, cardiovascular diseases; DBP, diastolic blood pressure; eGFR, estimated glomerular filtration rate; HbA1C, haemoglobin A1C; HDL, high-density lipoproteins; LDL, low-density lipoproteins; MIND-diet, mediterranean-DASH diet intervention for neurodegenerative delay; MVPA, moderate to vigorous physical activity; SBP, systolic blood pressure; TC, total cholesterol.

### Tailor-made online lifestyle advice for dementia risk reduction

Participants also receive an online tailor-made lifestyle advice targeting risk factors associated with dementia and following the Dutch guidelines for a healthy diet, alcohol consumption, physical activity, diabetes mellitus, renal dysfunction and cardiovascular health including cholesterol levels and BMI.^54–58^ For each risk and protective factor, information is given about (1) the norm (cut-off point for not having this risk factor), (2) the association between the risk factor and dementia and (3) lifestyle advice how to tackle this factor. The online lifestyle advice was tailored to the participants based on (1) the presence of risk factors, (2) the strength of the association between the risk factors and dementia^19 52^ and (3) the stages of change of the health behaviour-related risk factors (physical inactivity, diet, alcohol consumption, smoking behaviour, cognitive activity, social activity). The stages of change are determined by asking ‘Which statement fits best for you?’, where each answer option reflects one of the following stages of change: pre-contemplation, contemplation, preparation, action and maintenance.^33^ It is known that participants who are in the preparation and action stage are more willing to change their health behaviour, therefore lifestyle advice for these factors are given first.^33^

In case medically relevant findings are found, including untreated diabetes mellitus (glucose ≥7.0 mmol/L or (glucose ≥6.1 mmol/L and HbA1C>53 mmol/mol)), untreated renal dysfunction (estimated glomerular filtration rate (eGFR) ≤60 mL/min/1.73 m^2^) and increased risk for developing CVD (CVD risk ≥10% according to the Dutch Systematic Coronary Risk Evaluation (SCORE) formula^59^), participants receive, in addition to the online tailor-made lifestyle advice, a separate message in their personal inbox with the recommendation to contact their general practitioner to verify the results and discuss whether treatment is needed.

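### The printed health-profile and general-practitioner message rules conflict in three places: the Table 2 diabetes row, untreated HbA1c above 53 with glucose below 6.1, and an eGFR of exactly 60

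*Protocol article*

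**What the plan says.** All places are in the protocol article.

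- **One category per factor.** Under 'Personal health profile', each factor "is categorised into one of the following categories": room for improvement, remember to manage well, or keep this up. The profile is generated automatically.
- **Table 2, diabetes row.** 'Keep this up' is "Glucose<7.0 mmol/L and HbA1C≤53 mmol/mol", with no treatment condition. 'Remember to manage well' has two alternatives: "HbA1C≤53 mmol/mol and medical treatment) or (glucose<7.0 mmol/L and HbA1C>53 mmol/mol and medical treatment". The first clause of 'Room for improvement' is "HbA1C>53 mmol/mol and no medical treatment", at any glucose. Its other clauses are glucose ≥7.0 with HbA1c >53, and glucose ≥7.0 with HbA1c ≤53 if untreated.
- **Table 2, blood pressure row, for comparison.** 'Keep this up' is "DBP<90 mmHg and SBP<140 mmHg and no medical treatment". The cholesterol row has the same treatment exclusion.
- **Table 2, kidney row.** 'Keep this up' is "eGFR≥60 mL/min/1.73". The other two cells use <60, split by treatment.
- **Message rule**, under 'Tailor-made online lifestyle advice for dementia risk reduction'. The triggers include "untreated diabetes mellitus (glucose ≥7.0 mmol/L or (glucose ≥6.1 mmol/L and HbA1C>53 mmol/mol" and "untreated renal dysfunction (estimated glomerular filtration rate (eGFR) ≤60 mL/min/1.73".
- **Table 3, LIBRA definitions.** Diabetes is glucose >7.0 or HbA1c >53 (score +1.3). Renal dysfunction is eGFR ≤60 (score +1.1). Neither definition has a treatment term.

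**The concern.** Profile and message are part of the intervention, and the article presents the website as fully automatic and easy to take to other clinics. Rules meant for automation and reuse should give one output for one set of values. In three places they do not.

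The HbA1c discrepancy has the most practical weight. The profile tells an untreated participant with raised HbA1c that there is something to improve, yet the stated diabetes trigger does not tell that person to see the general practitioner. The eGFR discrepancy gives one person reassurance and a referral together. The double category for treated diabetes affects only which of two favourable labels is shown, and no message depends on it, but it can apply to any treated participant whose glucose and HbA1c are both in range.

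**Working it through.** The plan gives no figure to reproduce. The check applies the printed rules to every combination of values.

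**Diabetes.** The cut-offs in Table 2 and the message rule divide glucose into 3 bands (<6.1, 6.1 to <7.0, ≥7.0 mmol/L) and HbA1c into 2 (≤53, >53 mmol/mol). With treatment yes or no, that makes 3 × 2 × 2 = 12 regions. The message rule covers untreated participants only.

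| Glucose | HbA1c | Treated | Table 2 category | Message |
|---|---|---|---|---|
| <6.1 | ≤53 | no | Keep | no |
| <6.1 | ≤53 | yes | **Keep and Remember** | no |
| <6.1 | >53 | no | Room | **no** |
| <6.1 | >53 | yes | Remember | no |
| 6.1 to <7.0 | ≤53 | no | Keep | no |
| 6.1 to <7.0 | ≤53 | yes | **Keep and Remember** | no |
| 6.1 to <7.0 | >53 | no | Room | yes |
| 6.1 to <7.0 | >53 | yes | Remember | no |
| ≥7.0 | ≤53 | no | Room | yes |
| ≥7.0 | ≤53 | yes | Remember | no |
| ≥7.0 | >53 | no | Room | yes |
| ≥7.0 | >53 | yes | Room | no |

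1. *Category overlap.* 2 of 12 regions fall in two categories and 0 fall in none. Both overlaps are treated participants with glucose <7.0 and HbA1c ≤53. If 'Keep this up' also required no medical treatment, those two regions would be 'Remember to manage well' only, leaving 0 overlaps and 0 gaps.
2. *Message gap.* Four untreated regions are 'Room for improvement'. Three meet the message trigger. The fourth, glucose <6.1 with HbA1c >53, does not, although HbA1c >53 alone scores +1.3 in Table 3. For example, HbA1c 54 with glucose 6.0 gives no message, while HbA1c 54 with glucose 6.1 does. A trigger of untreated and (glucose ≥7.0 or HbA1c >53) covers 4 of 4 and adds no message outside 'Room for improvement'.

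**Kidney, untreated.**

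| eGFR | Table 2 (Keep if ≥60) | Message (≤60) | Table 3 (≤60) |
|---|---|---|---|
| 59 | Room | yes | +1.1 |
| 60 | **Keep** | **yes** | **+1.1** |
| 61 | Keep | no | 0 |

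3. *Boundary conflict.* Only the value 60 is affected. Using ≤60 throughout changes Table 2 alone and moves LIBRA by 0 points. Using <60 throughout would change the message rule and Table 3, and would lower LIBRA by 1.1 points for anyone at exactly 60.

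These are counts of rule regions and boundary values, not of participants.

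**The case against.** **A missed referral is not established.** A reader might infer that untreated participants with raised HbA1c and glucose below 6.1 go unreferred. The documents do not support that. The list of medically relevant findings is introduced as non-exhaustive. 'Dementia risk assessment' has laboratory results sent to a medical doctor, who checks them for deviating values. 'Adverse events' names diabetes as a reason for the message with no glucose condition. This objection stands as to consequence. It does not remove the discrepancy: the bracketed diabetes rule is explicit, and none of the three safeguards says that this pattern triggers the message.

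**The narrower trigger may be deliberate.** The message concerns findings for a doctor to verify, and the profile concerns lifestyle. Different thresholds could be a clinical choice. That is possible, though the article does not say so, and it is why the change needs clinical confirmation.

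**Table 3 is weak evidence.** It serves LIBRA scoring, has no treatment term, and differs openly from Table 2 elsewhere: weight is flagged from BMI 25 in Table 2, whereas obesity starts at 30 in Table 3. This is fair. Table 3 does not identify anyone as an untreated diabetic, and a difference between the two tables does not alone show an error. The category overlap lies within Table 2, and the other two conflicts lie between Table 2 and the message rule. For the same reason, the ≥ versus > differences between the tables at SBP 140, DBP 90 and glucose 7.0, and the differing lists of findings under the advice and adverse-event headings, are only points to clarify.

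**The prose could support either label for treated diabetes.** 'Personal health profile' also describes 'Keep this up' as covering factors under good control, and it ties well-managed diabetes to regular general-practitioner visits instead of medication. The prose is therefore ambiguous. The overlap remains whichever label is meant, and the blood pressure and cholesterol rows show how the table itself resolves such cases.

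**Conclusion.** The point holds as a minor matter, wrong as written. The printed rules put treated, in-range diabetes in two categories, leave one of four untreated 'Room for improvement' diabetes regions outside the stated message trigger, and contradict each other at an untreated eGFR of exactly 60.

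The conclusion rests on the rules as printed. The website code is not shown and may already be consistent, in which case only the text needs correcting. How many participants would be affected cannot be derived from the documents.

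A reader might also suspect that the trial's results are compromised. They are not: uptake depends on consent and completed assessment, the sample size does not use these rules, and LIBRA is scored from Table 3, which the recommended edits leave as it is.

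**What to change.** 1. In the 'Keep this up' cell of Table 2's diabetes row, add the condition of no medical treatment, as the blood pressure and cholesterol rows already do.
2. In the message rule, define the diabetes trigger as untreated with glucose ≥7.0 mmol/L or HbA1c >53 mmol/mol, once the clinical team confirms that the narrower rule was not intended. If it was intended, say so in one sentence.
3. Use one eGFR boundary. The simplest is 'Keep this up' >60 and the other two Table 2 kidney cells ≤60, which matches the message rule and Table 3. The clinical team should confirm this boundary too.
4. Check that the website logic matches the corrected text.

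The cost is two table rows, one clause and the logic check. Item 2 adds messages only for untreated participants with HbA1c >53 and glucose <6.1; their number is not given. No new data are needed, and neither the sample size nor the analysis changes.

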### Outcome measures and measurements

Participants are invited to fill in the online questionnaire at baseline and four times (3, 6, 9 and 12 months after baseline measurement) during 1 year follow-up. Physical examination, including the fasting blood sample for direct laboratory measurements, is only done at baseline and 12 months after baseline measurement (see online supplemental file 2). Data from the online questionnaires and physical examination are stored automatically in an electronic case report form (eCRF) data management programme, which is only accessible by the researchers involved in this study. Data from the direct laboratory measurement are entered manually in the eCRF data management programme. Every month, memory clinics are requested to provide information about (1) the number of eligible participants (eg, new cases of AD and VD), (2) the number of envelopes that are given away and (3) any difficulties with the recruitment of participants. In order to keep participating memory clinics involved in the study, every 3 months newsletters are sent around and memory clinics are contacted monthly to evaluate the uptake.

10.1136/bmjopen-2020-039439.supp2Supplementary data

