**Methods and analysis:**

Demin is a cluster randomised controlled trial, aiming to include 21 memory clinics of which 13 will be randomly allocated to the passive (poster and flyer in a waiting room) and 8 to the active recruitment strategy (additional personal invitation by members of the team of the memory clinic). We aim to recruit 378 participants (40–60 years) with a parent who is recently diagnosed with Alzheimer’s disease or vascular dementia at one of the participating memory clinics. All participants receive a dementia risk assessment (online questionnaire, physical examination and blood sample) and subsequently an online tailor-made lifestyle advice regarding protective (Mediterranean diet, low/moderate alcohol consumption and high cognitive activity) and risk factors (physical inactivity, smoking, loneliness, cardiovascular diseases (CVD), hypertension, high cholesterol, diabetes, obesity, renal dysfunction and depression) for dementia. The primary outcome is the difference in uptake between the two recruitment strategies. Secondary outcomes are change(s) in (1) the Lifestyle for Brain Health score, (2) individual health behaviours, (3) health beliefs and attitudes towards DRR and (4) compliance to the tailor-made lifestyle advice. Outcomes will be measured at 3, 6, 9 and 12 months after baseline. The effectiveness of this online tailor-made lifestyle programme will be evaluated by comparing Demin participants to a matched control group (lifelines cohort).

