### Risk and protective factors for dementia

Through the online questionnaire and physical examination, data on 13 currently known protective (ie, Mediterranean diet, low/moderate alcohol consumption, cognitive activity) and risk factors (ie, physical inactivity, smoking, loneliness, cardiovascular diseases, hypertension, high cholesterol, diabetes mellitus, obesity, renal dysfunction, depression) for dementia are collected.^6 19 52^ See table 1 for an overview of the assessment measures. The measurements of these risk and protective factors are described in online supplemental file 1.

10.1136/bmjopen-2020-039439.supp1Supplementary data

**Table 1 T1:** Assessment measures at baseline and follow-up

	Baseline	3 months	6 months	9 months	12 months
Risk and protective factors					
Smoking	Q	Q	Q	Q	Q
Physical inactivity (SQUASH, IPAQ)	Q	Q	Q	Q	Q
Mediterranean diet (FFQ)	Q	Q	Q	Q	Q
Alcohol consumption (FFQ)	Q	Q	Q	Q	Q
High cognitive activity (CRIq)	Q	Q	Q	Q	Q
Loneliness (de Jong Gierveld, 6-item)	Q	Q	Q	Q	Q
Cardiovascular diseases	Q	Q	Q	Q	Q
Obesity (body weight, height)	Q+PE	Q	Q	Q	Q+PE
Hypertension (SBP, DBP)	Q+PE	Q	Q	Q	Q+PE
High cholesterol (LDL, HDL, TC)	Q+FBS	Q	Q	Q	Q+FBS
Diabetes mellitus (glucose, HbA1C)	Q+FBS	Q	Q	Q	Q+FBS
Renal dysfunction (eGFR)	Q+FBS	Q	Q	Q	Q+FBS
Depression (CES-D)	Q	Q	Q	Q	Q

CES-D, centre for epidemiological studies depression scale; CRIq, cognitive reserve index questionnaire (adapted); DBP, diastolic blood pressure; eGFR, estimated glomerular filtration rate; FBS, fasting blood sample; FFQ, food frequency questionnaire; HbA1C, haemoglobin A1C; HDL, high-density lipoproteins; IPAQ, international physical activity questionnaire; LDL, low-density lipoproteins; PE, physical examination; Q, online questionnaire; SBP, systolic blood pressure; SQUASH, short questionnaire to assess health-enhancing physical activity; TC, total cholesterol.

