### Secondary outcomes

Secondary outcomes include:

(1) The change in LIBRA score. The LIBRA score has been validated among individuals in midlife and reflects an individual’s potential to reduce their risk on developing late-onset dementia.^52^ The LIBRA score consists of 12 currently known protective (ie, Mediterranean diet, low/moderate alcohol consumption, cognitive activity) and risk factors (ie, physical inactivity, smoking, CVD, hypertension, high cholesterol, diabetes mellitus, obesity, renal dysfunction, depression) for dementia and ranges from −5.9 (low risk for developing dementia) to 12.7 (high risk for developing dementia).

A one point increase in the LIBRA score is associated with a 19% higher risk for dementia.^52 60^ The definitions and corresponding scores for the three protective and ten risk factors for dementia are described in table 3.

**Table 3 T3:** Definition of risk and protective factors for dementia in the LIBRA score and corresponding scores

Modifiable risk factors		Definition	Score
Protective factors			
1	High cognitive activity	Score ≥50 points on the Cognitive Reserve Index questionnaire (leisure time activities) or hours of paid work ≥24 hours	−3.2
2	Mediterranean diet	MIND-diet score (0–14) =14 points	−1.7
3	Low/moderate alcohol consumption	Average number of glasses of alcohol a week ≤7 and number of glasses a day is: ≤3 glasses for women (no binge drinking), ≤4 glasses for men (no binge drinking)	−1.0
Risk factors			
4	Cardiovascular diseases	Presence of at least one of the follow diseases: history of angina pectoris, myocardial infarction, transient ischaemic attacks, stroke or peripheral arterial diseases	+1.0
5	Physical inactivity	Not fulfilling Dutch Norm for Physical activity defined as ≥150 min/week physical activity of moderate to vigorous intensity, measured with the SQUASH questionnaire	+1.1
6	Renal dysfunction	Estimated glomerular filtration rate ≤60 mL/min/1.73 m^2^	+1.1
7	Diabetes mellitus	Glucose (capillary blood) >7.0 mmol/L or HbA1c >53 mmol/mol	+1.3
8	High cholesterol	LDL >2.5 mmol/L or TC/HDL >5	+1.4
9	Smoking	Current smoker	+1.5
10	Obesity	BMI ≥30	+1.6
11	Hypertension	SBP >140 mmHg or DBP >90 mmHg	+1.6
12	Depression	Score ≥16 points on the Centre for Epidemiologic Studies Depression scale	+2.1

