### Statistical analyses

First, descriptive characteristics will be explored. The difference in uptake between the two recruitment strategies will be examined using multilevel logistic regression analyses in order to correct for clustering at memory clinic level. We will calculate the percentage with the corresponding 95% CI and use an alpha of 0.05 to test statistical significance.

The effectiveness of the online tailor-made lifestyle programme for DRR will be determined by, first comparing the change in LIBRA score, the individual risk factors and the MCLHB-DRR score between the active and passive recruitment strategy, and second comparing participants of the Demin study (active and passive recruitment strategy) to a control group consisting of Lifelines participants (large population-based cohort study (n>167 000)) (www.lifelines.nl)^64^ in outcome. Lifelines participants (age 40–60 years) with a parent with dementia will be matched (using propensity scores) on non-modifiable risk factors (age, gender and education) for dementia to participants of the Demin. Subsequently, multilevel analyses will be performed to examine the change in the LIBRA score and the individual health behaviours over time. In addition, possible confounding and interaction effects will be identified and corrected for in the analysis (eg, health literacy). We will calculate relative risks with 95% CIs and use an alpha of 0.05 to test significance.

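### Four LIBRA items cannot be scored by Table 3's definitions at 3, 6 and 9 months, so LIBRA change at those visits is not measurable as the protocol states

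*Protocol article*

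**What the plan says.** **Schedule.** Under Outcome measures and measurements, the online questionnaire is completed at baseline and at 3, 6, 9 and 12 months, but: "Physical examination, including the fasting blood sample for direct laboratory measurements, is only done at baseline and 12 months after baseline measurement". Table 1 agrees. For hypertension, cholesterol, diabetes, renal function and body weight it lists the questionnaire plus an examination or blood sample at baseline and 12 months, and the questionnaire alone at 3, 6 and 9 months.

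**Definitions.** Table 3 (Secondary outcomes) scores hypertension as "SBP >140 mmHg or DBP >90 mmHg", high cholesterol as "LDL >2.5 mmol/L or TC/HDL >5", diabetes as "Glucose (capillary blood) >7.0 mmol/L or HbA1c >53 mmol/mol", and renal dysfunction by an eGFR cut-off. None of the four has a self-report or medication alternative. Obesity is a BMI cut-off with no stated mode of measurement.

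**Use.** The abstract lists LIBRA change as the first secondary outcome and then says: "Outcomes will be measured at 3, 6, 9 and 12 months after baseline". Statistical analyses says that "multilevel analyses will be performed to examine the change in the LIBRA score and the individual health behaviours over time". LIBRA change is compared first between active and passive recruitment, then between Demin participants and matched Lifelines participants.

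**The concern.** The outcome definition, the measurement schedule and the stated outcome times cannot all be met. At three of the five visits, a third of the LIBRA items (4 of 12) have no value of the kind that Table 3 requires.

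Filling the gap in the LIBRA series carries a cost:

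- **Questionnaire answers replace measurements.** A raised value that is found on testing but not reported loses its points at 3, 6 and 9 months and regains them at 12 months. That looks like early benefit followed by relapse, with no change in the participant.
- **Items are omitted and count as absent.** The pattern is the same, and larger.
- **Baseline values are carried forward.** Real change in these four items cannot show before 12 months.

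LIBRA is the main summary of whether the programme changes risk, so the source of its components should not differ between the visits being compared.

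**Working it through.** **1. Reproduce the stated range.** Weights from Table 3:
- Protective: -3.2 - 1.7 - 1.0 = -5.9.
- Risk: 1.0 + 1.1 + 1.1 + 1.3 + 1.4 + 1.5 + 1.6 + 1.6 + 2.1 = 12.7.

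Both match the protocol. The width is 12.7 + 5.9 = 18.6 points.

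**2. Share that cannot be scored at 3, 6 and 9 months.** Hypertension 1.6 + cholesterol 1.4 + diabetes 1.3 + renal 1.1 = 5.4 points.
- 5.4/18.6 = 29% of the range.
- 5.4/12.7 = 42.5% of the risk points.

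Obesity (1.6) can still be scored, but its source changes to self-reported weight. With it, 7.0 points (7.0/18.6 = 38%) change source or lose it.

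**3. Possible spurious shift if questionnaire answers are substituted.** With no true change and no false-positive reports, the shift in mean LIBRA at 3, 6 and 9 months is

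s = -Σ weight × prevalence × (1 - sensitivity).

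The documents give neither prevalence nor sensitivity. Assumed prevalence ranges: hypertension 15-40%, high cholesterol 40-85%, diabetes 2-8%, renal dysfunction 1-3%.
- Σ weight × prevalence, low: 1.6×0.15 + 1.4×0.40 + 1.3×0.02 + 1.1×0.01 = 0.84.
- Σ weight × prevalence, high: 1.6×0.40 + 1.4×0.85 + 1.3×0.08 + 1.1×0.03 = 1.97.

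| Sensitivity of questionnaire | Shift s (points) |
|---|---|
| 1.0 | 0 |
| 0.9 | -0.08 to -0.20 |
| 0.5 | -0.42 to -0.98 |
| 0 (items scored absent) | -0.84 to -1.97 |

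At the protocol's 19% per point, 1 - 1.19^s gives an apparent risk reduction of about 1.4-3.4% at sensitivity 0.9 and 7.0-15.7% at 0.5.

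**4. Where the shift would show.** Take the spurious series as 0, s, s, s, 0 at months 0, 3, 6, 9, 12.
- *Straight-line slope, complete data:* month deviations are -6, -3, 0, 3, 6, so the numerator is s(-3 + 0 + 3) = 0. There is no bias.
- *Straight-line slope, last seen at 9 months:* deviations are -4.5, -1.5, 1.5, 4.5. The numerator is s(-1.5 + 1.5 + 4.5) = 4.5s and the denominator is 45, so the slope is 0.1s per month.
- *Mean of four follow-ups against baseline:* (s + s + s + 0)/4 = 0.75s.
- *Contrast of 3, 6 or 9 months with baseline:* s in full.
- *12 months against baseline:* 0.
- *Active against passive:* the difference between the two groups' shifts, which is about 0 if prevalence, reporting and retention are alike.

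**5. Range of a same-source score.** Removing the four measured items and obesity leaves risk points 12.7 - 7.0 = 5.7, hence -5.9 to 5.7. Keeping obesity from self-reported weight at every visit gives -5.9 to 7.3.

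**The case against.** A reader might infer that the plan fits LIBRA as one five-visit series and will therefore show artefactual change. The documents do not support that. Statistical analyses and Secondary outcomes name no visits for LIBRA, and the abstract's sentence on timing covers all outcomes together. Restricting LIBRA to baseline and 12 months, or treating interim LIBRA as missing, is compatible with the text and produces no artefact. Item measurement is referred to a supplement that is not shown, and an interim rule may be there.

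A reader might also infer that anyone with an unrecognised raised value loses points at 3 months. After baseline, however, each participant receives a health profile covering every factor, and relevant findings trigger a message to consult a general practitioner. Many will know their results by 3 months. Suppose instead that reporting rates were low: 15-20% reporting high cholesterol against 50-80% on testing, and 10-15% against 20-30% for blood pressure. These assumptions give 0.65 to 1.08 points, an apparent 11-17% lower risk. That is an unfavourable case rather than an expected one. With the same prevalences and 90% correct reporting, those two items give 0.1×(1.6×0.2 + 1.4×0.5) = 0.10 to 0.1×(1.6×0.3 + 1.4×0.8) = 0.16 points.

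Finally, the artefact does not survive every analysis: it is zero in a complete-data linear slope and largely cancels between the randomised groups.

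These points limit the size and certainty of the consequence, but they leave the conflict in place. Table 3 allows only measured values for four items, the schedule does not supply them at three visits, and the abstract includes those visits as outcome times. Cancellation between groups also cannot be taken for granted, because the Introduction itself expects that passive recruits may drop out less.

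**Conclusion.** The point holds as an internal contradiction with a conditional consequence. By Table 3, four LIBRA items worth 5.4 of 18.6 points (29%) cannot be scored at 3, 6 and 9 months, and obesity changes source; this follows from the document alone. Whether a spurious change then appears depends on a scoring rule that the article does not give.

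If questionnaire answers are used, the interim fall is about 0.1-0.2 points when about 90% of raised values are reported correctly, and up to about 1 point when about half are. Both figures rest on assumed prevalences and full specificity. Scoring the items as absent would give more.

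The bias would affect visit-specific contrasts and follow-up averages, and slopes where 12-month data are missing. It need not cancel against Lifelines, for which the article gives no visit schedule. LIBRA is a secondary outcome, so uptake and the sample size are not touched.

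**What to change.** - Define the LIBRA outcome as the change from baseline to 12 months, scored by Table 3 at both visits, with BMI from measured height and weight at both. Use it for the active-passive comparison and for the Demin side of the Lifelines comparison.
- For 3, 6 and 9 months, analyse a separately named questionnaire-only sub-score: cognitive activity, diet, alcohol, cardiovascular disease, physical inactivity, smoking and depression (range -5.9 to 5.7). Compute it from the same source at all five visits. Obesity may be added (range to 7.3) if self-reported weight is used at every visit, including baseline and 12 months.
- Amend the abstract's statement on outcome times, and name the visits that enter each multilevel model.

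The cost is wording: no new visits, tests or participants. What is given up is a full-LIBRA time course between baseline and 12 months. The protocol's 19% per point is stated for the full score and should not be attached to the sub-score.
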